## Randomisation, blinding and treatment allocation

Block-randomization will be performed via the REDCap randomization module on a 1:1:1 basis for every participating centre.

## Study procedures

Before the start of the data collection, a refamiliarization session for all three nerve block procedures will be hosted in each individual center. In this refamiliarization session, an expert in POCUS will provide theoretical and practical training in block placement for each of the three blocks, and will test and log the skill level of the participating physicians in a dedicated training log. Only physicians who are able to perform all three blocks in line with the NYSORA guidelines are eligible for participation in the study.^31-33^

[figure not shown]

**Figure 2**. Timeline of the study procedure, showing which data will be collected at what time point.

Data will be gathered at 6 different time points (T1-T6). *Figure 2* shows a detailed timeline of data collection.

Pre-block characteristics (demographic data (age, sex, weight), ASA score, pain scores (VAS) during rest and light elevation of the affected leg, type of fracture, analgesics administered before hospital admission (including medication routinely used by the patient), block characteristics (type of block, visualization of landmarks, amount- and type of LA administered, timing of block placement), and post-block characteristics (total amount of opioids administered in the first 12 hours after block administration and (S)AE’s) will be reported in an electronic case report form (appendix IV).

The primary endpoint, quality of recovery, will be measured either 6-8 hours post-block, or pre-OR (whichever one comes first) with the Quality of recovery-15 (QoR) patient-reported outcome questionnaire that measures the quality of recovery after surgery and anaesthesia.^34^ To ensure patients will be adequately rested for their operation, QoR-15 registration will be postponed until the next morning for blocks placed between 17.00 and 22.00 hours, as QoR-15 registration would then fall between 23.00 and 6.00. The QoR-15 questionnaire can be found in the appendices (*Appendix III*). Previous studies have shown a good convergent validity between the QoR-15 and the visual analog scale (VAS). Additionally, validity of the QoR-15 is supported by a negative correlation with duration of surgery and duration of hospital stay, and the QoR-15 shows excellent internal consistency, split-half reliability, test–retest reliability, and responsiveness.^34^

As the QoR-15 questionnaire needs to be collected 6-8 hours after block administration, or before admittance to the OR (whichever one comes first), a member of the research team will visit the patient at their designated department (surgery or orthopaedics) to collect this data when 6-8 hours have passed since block administration, or pre-OR.

## Withdrawal of individual subjects

Subjects can leave the study at any time for any reason if they wish to do so without any consequences. The investigator can decide to withdraw a subject from the study for urgent medical reasons.

## Replacement of individual subjects after withdrawal

Not applicable.

## Premature termination of the study

Can be performed for unforeseen indications as stated under safety reporting.

# SAFETY REPORTING

## Temporary halt for reasons of subject safety

In accordance to section 10, subsection 4, of the WMO, the investigator will suspend the study if there is sufficient ground that continuation of the study will jeopardise subject health or safety. The investigator will notify the accredited METC without undue delay of a temporary halt including the reason for such an action. The study will be suspended pending a further positive decision by the accredited METC. The investigator will take care that all subjects are kept informed.

## AEs, SAEs and SUSARs

### Adverse events (AEs)

Adverse events are defined as any undesirable experience occurring to a subject during the study, whether or not considered related to the intervention. All adverse events reported spontaneously by the subject or observed by the investiga­tor or staff will be recorded. All three of the procedures (PENG, FICB, FNB) are common clinical practice and carry the same side effects related to the use of local anaesthetics.

AE’s related to the use of local anaesthetics are:

- Soreness at the injection site;
- Tingling feeling;
- Ringing in the ears;
- Headache, dizziness, blurred vision and/or confusion;
- Twitching muscles or shivering;

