**Secondary Objective(s):**

- To compare pre-operative pain scores 15 min, 30 min, and 1 hour post-block placement in patients receiving PENG, FICB and FNB in the ED.
- To compare the amount of rescue medication, calculated as mg/hour given IV in the ED after block placement or SC/IO in the ward during the first 12 hours after block placement or until operation.
- To compare complications of block placement in patients receiving PENG, FICB and FNB in the ED in the first 24 hours after block placement.

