# STUDY DESIGN

This study will be a non-blinded, multicentre Randomized Controlled Trial (RCT), conducted in the ED of the MCL and other cooperating hospitals. Patients with a confirmed proximal- or neck of femur fracture are randomized to one of three treatment arms: FICB, FNB or PENG. After randomization regional anaesthesia is provided according to a standardized protocol and pain scores are measured at fixed time intervals. Patient reported outcomes are measured with a validated (QoR-15) questionnaire either 6-8 hours after block administration or before admittance to the operating room (OR), whichever one comes first. A flowchart of the study design can be found below (*Figure 1*).

**Figure 1**. Flowchart of the study design.

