### Secondary study parameters/endpoints (if applicable)

- - Pre-operative pain scores at 15 min-, 30 min-, and 1 hour post-block placement.
  - The amount of rescue medication calculated as mg/hour given IV in the ED after block placement or SC/IO in the ward during the first 12 hours after block placement or until operation.
  - Number and type of adverse and serious adverse events.

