***Zie volgende pagina!***

**Data te verzamelen 12 uur na block procedure**

Opioïden toegediend na block (incl. dosering)

..…..…………………………………………………..…..…………………………………………….

..…..…………………………………………………..…..…………………………………………….

..…..…………………………………………………..…..…………………………………………….

Tijdstip meting opioïden: .... : .… uur *(zoals 9:30, op het moment dat het half 10 in de ochtend is)*.

Hoeveelheid benodigde opioïden: ……. mg/uur

(S)AE’s voorgekomen (omcirkel) : Ja / Nee

Indien “Ja”, specificeer : …..…………………………………………………

..…..…………………………………………………..…..…………………………………………….

..…..…………………………………………………..…..…………………………………………….

Is er sprake van een verband tussen LA en SAE? (omcirkel) Ja / Nee

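### Adverse events are compared between blocks in an open trial, but the expected mild symptoms are recorded only if volunteered or noticed; a uniform symptom checklist would be a cheap improvement

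*Protocol*

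**What the plan says.** The Study Design section of the protocol states: "This study will be a non-blinded, multicentre Randomized Controlled Trial (RCT"). Safety is one of the things compared. A secondary objective reads "To compare complications of block placement in patients receiving PENG, FICB and FNB in the ED in the first 24 hours after block placement", and section 5.1.2 lists the endpoint as "Number and type of adverse and serious adverse events".

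Section 6.2.1 sets the method of capture: "All adverse events reported spontaneously by the subject or observed by the" investigator or staff are recorded. It then lists the reactions expected from local anaesthetics, in five lines: soreness at the injection site, tingling, ringing in the ears, a group of headache, dizziness, blurred vision and confusion, and muscle twitching or shivering. Section 6.2.2 lists seven kinds of serious event and says that all serious events are documented.

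In Appendix IV, the block of the form headed "Data te verzamelen 12 uur na block procedure" has a single item for adverse and serious adverse events, "voorgekomen (omcirkel) : Ja / Nee", with free text if the answer is yes. The protocol describes no prompted symptom question and no blinded assessor of adverse events. Section 6.2.3 names an independent expert, but only for judging whether a serious event is related to the local anaesthetic.

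**The concern.** Whether a patient mentions tingling, ringing or dizziness depends largely on whether someone asks. Here the patient and the staff both know which block was given, and nothing makes the asking the same in each arm. If one arm is asked more often or more closely, it will show more mild events even when the true rates are equal. The reverse can also happen: a true difference can vanish when the arm with more symptoms is asked less.

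This is fixed at data collection. An analysis plan can choose the unit, the test and the summary, but it cannot recover symptoms that nobody asked about. It therefore matters here although the statistical analysis plan is not at hand.

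At stake is one secondary comparison, mainly its mild and subjective part. The primary endpoint is not touched, and deaths, cardiac arrests and similar events would be recorded whatever the arm.

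**Working it through.** **Planning figure.** The protocol gives no planning figure for safety. The number per arm comes from section 3.4, for the QoR-15: difference 6.0, SD 10, power 0.9, two-sided 0.05. By the normal formula, n = 2 × (1.960 + 1.282)² × (10/6)² = 58.4, so 59 per arm. The t-test version gives 59.35, so 60 per arm, 3 × 60 = 180, and 180 × 1.1 = 198. The stated figures reproduce, and 60 per arm is used below.

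**Assumed inputs (none is in the protocol).** The true proportion of patients with a symptom, p, is the same in both arms, at 5%, 10%, 20% or 30%. The fraction of these patients who are recorded is 50% in one arm and 70% in the other, or 40% and 80%.

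**Method.** The recorded proportion in an arm is p times its recording fraction. Two arms of n = 60 are compared with z = (p̂₁ − p̂₂) / √(2 p̄(1 − p̄)/60), and |z| > 1.96 is called significant. The chance of this was found by exact enumeration of both binomial distributions.

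**Example, p = 20%, recording 50% against 70%.**
- Recorded proportions: 0.20 × 0.50 = 0.10 and 0.20 × 0.70 = 0.14, a spurious difference of 0.04.
- Pooled proportion 0.12; standard error √(2 × 0.12 × 0.88/60) = 0.0593; difference needed for significance 1.96 × 0.0593 = 0.116.
- Normal approximation: (0.116 − 0.04)/0.0592 = 1.29, an upper tail of about 10%. Exact: 10.0%.

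**Example, p = 20%, recording 40% against 80%.** Recorded 0.08 and 0.16, difference 0.08; (0.116 − 0.08)/0.0589 = 0.62, about 27%. Exact: 26.5%.

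**Chance of a false significant difference, two arms of 60:**

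| True rate, both arms | 50% v 70% recorded | 40% v 80% recorded |
|---|---|---|
| 5% | about 4% | about 7% |
| 10% | about 7% | about 14% |
| 20% | about 10% | about 27% |
| 30% | about 13% | about 40% |

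With equal recording at a 20% rate, the figure is about 5%.

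**Three arms.** A separate simulation used a chi-square test on patients with at least one event, 60 per arm, and equal true rates of 20% to 30%. Recording 90% in one arm and 70% in the other two gives false significance in about 9% to 12% of trials; 90% against 50% gives about 26% to 39%. Counting patients rather than events therefore does not cure unequal recording.

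**Hiding a difference.** True rates of 28% and 20%, recorded at 50% and 70%, both become 14% (0.28 × 0.50 = 0.20 × 0.70 = 0.14).

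**Time windows.** The secondary objective covers 24 hours after the block. The form collects events under a 12-hour heading. Events between 12 and 24 hours fall within the objective but have no stated place on the form.

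**The case against.** **Capture is not purely passive.** Section 6.2.1 also covers events seen by investigator or staff, and the yes/no item stands on every patient's form at the same time point. Twitching, shivering and confusion can be observed, hypotension has a numeric threshold, and all serious events are documented. This stands, and it rules out saying that the endpoint rests on spontaneous reports alone. It weakens the concern only a little for subjective symptoms, because the observers know the block too and the item carries no prompts.

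**Nothing shows that recording will differ by arm.** A reader might infer that PENG, as the more recent block, will draw closer attention. The protocol does not say so: it calls all three blocks standard care and requires each participating physician to be able to perform all three. The possibility is open, but its direction and size are unknown.

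**The figures depend on assumed rates.** This stands. At a true rate of 5% with 50% against 70% recorded, false significance is about 4%, so there is no inflation above the nominal level. It becomes material only if symptoms are common or recording is very unequal.

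**Event counting.** Because section 5.1.2 speaks of a number of events and the listed reactions overlap, a reader might infer that several symptoms of one patient will be tested as independent observations. The documents do not support this. The endpoint names no counting unit, the form yields one yes/no per patient, and the Statistical Analysis section does not commit to an event-level test. A statistical analysis plan could settle the unit.

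**Conclusion.** The point holds as a modest, cheap improvement to how mild adverse events are ascertained. A comparative safety endpoint in an open trial is fed by volunteered reports, observation by unblinded staff and one unprompted item, and no later analysis can make up for symptoms that were not asked about. The effect could be nil or substantial: about 4% to 13% false significance under the milder assumed imbalance and about 7% to 40% under the stronger one, for true rates of 5% to 30%. These are illustrations, not estimates, because both the rates and the recording fractions are assumed. The concern applies to the subjective symptoms in section 6.2.1 and hardly at all to hard serious events. The counting unit is a matter of clearer wording, not a demonstrated analysis error. The mismatch between the 24-hour objective and the 12-hour form is plain from the text and needs correcting in any case.

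**What to change.** - **Section 6.2.1 and Appendix IV:** add a fixed yes/no checklist of the symptoms already listed in 6.2.1, asked in the same words in all three arms at the 1-hour pain reading and at the QoR-15 visit. Keep spontaneous and observed reports as an addition.
- **Section 5.1.2:** state that results are reported as the number of patients with at least one event, overall and by type.
- **Secondary Objectives and Appendix IV:** reconcile the 24-hour window with the 12-hour collection. The two checklist contacts do not in themselves cover 24 hours, so this needs its own decision.

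The cost is a short tick list in the eCRF at two contacts that the protocol already provides for. More mild events will be recorded in every arm. Because patients and staff remain unblinded, the checklist reduces the bias but does not remove it, and the report should say so.

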### Serious adverse events (SAEs)

A serious adverse event is any untoward medical occurrence or effect that

- results in death;
- is life threatening (at the time of the event);
- requires hospitalisation or prolongation of existing inpatients’ hospitalisation;
- results in persistent or significant disability or incapacity;
- any other important medical event that did not result in any of the outcomes listed above due to medical or surgical intervention but could have been based upon appropriate judgement by the investigator.

*An elective hospital admission will not be considered as a serious adverse event.*

SAE’s related to the use of local anaesthetics, although very uncommon, are:

- Local Anaesthetic Systemic Toxicity (LAST);
- Bleeding from accidental femoral artery puncture;
- Nerve injury;
- Anaphylaxis;
- Cardiac arrest;
- Any arrhythmia;
- Hypotension (systolic blood pressure < 90 mmHg or a drop of >20% compared to baseline).

In case of SAEs due to systemic toxic effect of the used anaesthetics, physicians are supposed to handle by using their existing local LAST-protocol (Appendix I: example of a LAST protocol). This is exactly the same procedure for all three block types and is therefore not different to the standard way of care. In the even more unlikely case of an anaphylactic reaction to ultrasound gel or local anaesthetic, the hospitals local protocol ‘Anaphylaxis’ (‘Anafylaxie’) will be used (Appendix II: example of an anaphylaxis treatment protocol).

The investigator will document all SAEs, including those related to the underlying condition (hip fracture). An overview of SAEs will be provided in the annual overview report. SAE’s potentially related to the use of LA, from now on named SAR (Serious Adverse Reaction), will be reported as mentioned in paragraph 6.2.3. As the anticipated number of SAE’s due to the underlying condition (hip fracture) is high, SAE’s that are directly relatable to hip fractures will be exempt from reporting to the Toetsingonline portal.

### Suspected Unexpected Serious Adverse Reactions (SUSARs)

An SAE that occurs during research with an investigational product (LA in this study) may be a SAR or a SUSAR (Suspected Unexpected Serious Adverse Reaction).

An SAE is a SAR if there is a certain degree of probability that the SAE is a harmful and undesired reaction to LA, regardless of the administered dose. If the SAR is unexpected it is called a SUSAR. Following documentation of an SAE, the investigator and the independent expert will determine whether the SAE could be related to LA use. Figure 3 provides definitions of relatedness.

In case it is decided that the SAE is related to LA use following the definitions found in Figure 3 (thus being a SUSAR), it will be reported by the investigator through the web portal *ToetsingOnline* to the accredited METC that approved the protocol, within 7 days of first knowledge for SUSARs that result in death or are life threatening followed by a period of maximum of 8 days to complete the initial preliminary report. All other SUSARs will be reported within a period of maximum 15 days after first knowledge of the serious adverse events.

[figure not shown]
As the anticipated number of SAE’s due to the underlying condition (hip fracture) is high, SAE’s that are directly relatable to hip fractures will be exempt from reporting to the Toetsingonline portal.

**Figure 3**. Definitions of relatedness.

SAE’s are certainly not related to LA use when they occur more than 12 hours after block administration, as the LA used in this study work for 8-12 hours.

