**Nature and extent of the burden and risks associated with participation, benefit and group relatedness:**

Although PENG, FICB and FNB are overall safe when performed correctly, there are some risks associated with these procedures. These risks include: bleeding (1-2% chance), infection, damage to surrounding structures, (permanent) nerve injury, and intravascular uptake of local anesthetic resulting in systemic toxicity (LAST). In addition, there is a 5-10% chance that the block provides suboptimal analgesia with the need for additional analgesics. Important to note is that PENG, FICB and FNB are all standard care in the ED. However, since all included types of regional anesthesia in the setting of traumatic femur fractures are part of well-established clinical practice, there is no additional risk for the patients participating in this study. **INTRODUCTION AND RATIONALE**

An aging population will result in a growing prevalence of hip fractures.^1,2^ Hip fractures pose an increased risk of mortality, morbidity, and functional impairment.^3^

Adequate perioperative pain reduction is of utmost importance as pain is an important factor influencing complication rates, posing a significant risk for decreased functional outcomes, prolonged time to mobilization and longer hospital stay.^4,5^ Systemic analgesia is commonly used in the pain management of patients with hip fractures, including opioids (e.g. morphine or fentanyl).^6^ However, opioids are associated with adverse events such as delirium, vomiting, pruritus and respiratory depression, which are even more common in older patients.^7,8^ Additionally, opioids are highly addictive, as illustrated by the ongoing worldwide opioid crisis.^9^

An alternative method to obtain adequate analgesia is the use of regional nerve blocks. Nerve blocks have several advantages over systemic analgesia. First, they may provide superior analgesia.^5^ Second, they contribute to a reduction in opioid use and opioid-related adverse events, and thereby decrease the risk of delirium and cognitive dysfunction.^10-12^ Previous research has shown that survival and length of hospital stay are both positively associated with the use of regional anesthesia in hip fractures.^13^ Recent guidelines therefore advise to use regional anaesthetic techniques for pain management in hip fractures.^14-16^

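### Causality of serious harm is judged only against the local anaesthetic, not the randomised block procedure, so procedural complications cannot be systematically attributed and some lack a clear expedited-reporting route

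*Protocol*

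**What the plan says.** **Objective and endpoint.** The third secondary objective in section 1 is "To compare complications of block placement in patients receiving PENG, FICB and FNB in the ED", within 24 hours of placement. The matching endpoint in section 5.1.2 is "Number and type of adverse and serious adverse events", with no condition on relatedness. Section 6.2.1 records AEs regardless of relation to the intervention, and section 6.2.2 has all SAEs documented.

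**Causality.** Section 6.2.3 takes the drug as the product under study: "An SAE that occurs during research with an investigational product (LA in this study) may be a SAR or a SUSAR". It defines the reaction accordingly: "An SAE is a SAR if there is a certain degree of probability that the SAE is a harmful and undesired reaction to LA". The question put to the assessors is the same: "the investigator and the independent expert will determine whether the SAE could be related to LA use". Expedited reporting follows from the answer: "In case it is decided that the SAE is related to LA use following the definitions found in Figure 3 (thus being a SUSAR"). The section closes by ruling out a relation to LA for any SAE that occurs more than 12 hours after the block, on the ground of how long the LA acts.

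**Case report form (Appendix IV).** The page to be completed 12 hours after the block asks whether any (S)AE occurred, asks for a specification, and then puts one yes/no relatedness question: "Is er sprake van een verband tussen LA en SAE", that is, whether LA and SAE are linked.

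**Named procedural risks.** The Summary says of the three blocks: "These risks include: bleeding (1-2% chance), infection, damage to surrounding structures, (permanent) nerve injury", followed by systemic toxicity.

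**The concern.** The arms differ in needle target and technique. The choice of LA is left to the centre, and Table 1 is not split by block. Section 6.2.1 itself says that the three procedures share the side effects of LA. Attribution to LA is therefore the attribution least suited to separating the arms, and it is the only one collected. The harms that the objective names, those of placing the block, have no causality question of their own.

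Two things are at stake. First, the report could not give a count by arm of complications judged to be due to the block, because the form never asks. A later analysis plan cannot recover a judgement that was not recorded. Second, a serious needle injury could be classed as unrelated under one section and related under another, and so be expedited or not depending on the reader.

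**Working it through.** The point is textual, so the check sets the sections side by side.

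**Step 1: is there any route other than LA?** Product, reaction definition, assessors' question, reporting trigger and form item all name LA only. Because 6.2.3 treats an SAE judged LA-related as a SUSAR, that one judgement is the gate to expedited reporting. The form asks no relatedness question for non-serious AEs.

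**Step 2: what happens to each named harm if it is serious?**

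| Event | Risk in Summary | On 6.2.2 list of LA-related SAEs | Reaction to LA under 6.2.3 | Result |
| --- | --- | --- | --- | --- |
| Systemic toxicity | yes | yes | yes | route clear |
| Bleeding from arterial puncture | yes, as bleeding | yes | no, on its plain words | sections conflict |
| Nerve injury by needle | yes, as nerve injury | yes, as nerve injury | no, on its plain words | sections conflict |
| Infection | yes | no | no | no clear route |
| Damage to surrounding structures | yes | no | no | no clear route |

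The last two are also absent from the AE list in 6.2.1.

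**Step 3: timing.** The objective covers 0 to 24 hours. The 12-hour statement leaves 24 − 12 = 12 hours, half of that window, in which any SAE is unrelated to LA by rule. The reason given is duration of drug action, which does not bear on a haematoma, an infection or a needle injury. With no procedural route in the text, a procedural SAE first seen in those 12 hours has no clear path to expedited reporting.

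**Step 4: is anything removed from the comparison?** No. The endpoint is a count by number and type, and the form takes the event and its specification before the LA question. A haematoma answered as not LA-related still counts.

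**Step 5: scale.** Section 3.4 gives 180 × 1.10 = 198 patients, or 198 / 3 = 66 per arm. At the Summary's bleeding risk:

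- 198 × 0.01 = 1.98 and 198 × 0.02 = 3.96 bleeds in total;
- 66 × 0.01 = 0.66 and 66 × 0.02 = 1.32 per arm.

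These are bleeds of any severity. The protocol gives no figure for serious bleeds, or for infection, structural damage or nerve injury.

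**The case against.** The strongest reply is that the safety comparison does not use relatedness at all. Events are recorded, typed and counted by arm whatever the LA answer. That stands. A reader might infer that needle and technique complications fall outside the safety comparison, and the documents do not support this. Nor do they support the inference that the aim cannot be answered because fracture events swamp the rest: section 6.2.2 says only that many fracture-related SAEs are expected, gives no number, and events are reported by type.

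A second reply is that the 6.2.2 list gives bleeding and nerve injury a route, since SAEs potentially related to LA use are to be reported under 6.2.3, and every documented SAE goes to the investigator and the independent expert. This also stands in part. It defeats the inference that all serious procedural harm escapes expedited reporting. It does not remove the conflict with the 6.2.3 definition, and it does not help unlisted harms or events after 12 hours.

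Third, the definitions of relatedness are in Figure 3, which is not shown and might mention the procedure. That limits certainty, although the surrounding text and the form refer only to LA.

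Fourth, LA exposure is not identical across arms: the injected volume is 15 ml for FNB and 40 ml for FICB and PENG. LA-related harm could therefore differ by arm, and the LA question is worth keeping.

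Fifth, the trial is not blinded, so a relatedness judgement can be coloured by knowledge of the arm. This is a good reason not to make relatedness the endpoint.

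**Conclusion.** The concern holds in a limited form. Causality is assessed against LA only, although the procedure is what is randomised and what the safety objective concerns. Procedural harms remain in the all-event count but cannot be systematically attributed to block placement. Sections 6.2.2 and 6.2.3 let the same bleed or nerve injury be classified either way. Serious infection, serious structural damage, and procedural SAEs after 12 hours have no clear expedited route.

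The expected number of affected events is small and cannot be fixed from the protocol. The 2 to 4 bleeds are of any severity and serve only as context. The primary endpoint and the sample size are untouched. The conclusion assumes that Figure 3 follows the text around it. The change should be made because it is cheap and corrects both a contradiction and a gap in safety attribution.

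**What to change.** - In 6.2.2, 6.2.3 and the form item, widen the causality wording from LA to *related to the block procedure or to the LA*. Check that Figure 3 matches.
- Ask the question for AEs as well as SAEs.
- Add the procedural risks named in the Summary, including infection and damage to surrounding structures, to the event lists.
- Reconcile the 6.2.2 list with the 6.2.3 definition, and reconcile the 12-hour statement and the 12-hour form page with the 24-hour objective.
- Keep the count of all (S)AEs by number and type as the endpoint in 5.1.2, because relatedness is judged unblinded. Report block- or LA-related complications by arm beside it.

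The cost is wording in a few safety passages, one changed form item, and a few more events through causality review and possibly expedited reporting.

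### Block complications are to be compared over 24 hours, but the only scheduled (S)AE entry shown is at 12 hours, and a fixed rule rules out drug-relatedness for any SAE after that

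*Protocol*

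**What the plan says.** Section 1 of the protocol, under the secondary objectives, sets the safety comparison: "To compare complications of block placement in patients receiving PENG, FICB and FNB in the ED in the first 24 hours after block placement". The matching endpoint in section 5.1.2 is the number and type of adverse and serious adverse events. It gives no time window and no restriction to related events.

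The case report form in Appendix IV has one (S)AE item (yes/no, with free text) and one yes/no question on a link between the LA and the SAE. Both stand on the page headed "Data te verzamelen 12 uur na block procedure", that is, data to be collected 12 hours after the block. The form as shown has no later page.

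Section 6.2.3 states that SAEs are "certainly not related to LA use when they occur more than 12 hours after block administration", and gives one reason: "as the LA used in this study work for 8-12 hours". The same section says that "the investigator and the independent expert will determine whether the SAE could be related to LA use", and sets the threshold: "An SAE is a SAR if there is a certain degree of probability that the SAE is a harmful and undesired reaction to LA". Neither of these two statements carries a time limit.

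Section 6.2.2 lists SAEs that the protocol regards as related to local anaesthetic use. The list includes nerve injury and "Bleeding from accidental femoral artery puncture".

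**The concern.** Two separate problems arise, and they have different consequences.

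The first is capture. If complications are to be compared over 24 hours but the form asks about them at 12, the second half of the window depends on unprompted reports. With few events expected, uneven or incomplete ascertainment in that half can alter what the comparison shows. Safety is part of the stated aim, so the comparison should be made on data collected alike in every arm.

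The second is attribution. A rule that settles relatedness by the clock takes the decision away from the people whom the protocol asks to make it. Under section 6.2.3 the finding that an SAE is related to LA use triggers the 7-day or 15-day report to the ethics committee. A rule that fixes relatedness in advance therefore also fixes reporting.

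**Working it through.** No figure in the plan has to be reproduced here. The check sets the time windows side by side.

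**Windows stated**

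| Item | Place in the protocol | Window |
| --- | --- | --- |
| Comparison of block complications | Section 1, secondary objectives | 24 h |
| (S)AE endpoint | Section 5.1.2 | none stated |
| Scheduled (S)AE entry and LA-SAE question | Appendix IV | 12 h |
| SAE can be LA-related | Section 6.2.3 | up to 12 h |
| Duration of action given as the reason | Section 6.2.3 | 8-12 h |
| Recording of AEs and SAEs in general | Sections 6.2.1, 6.2.2 | no limit stated |
| SUSAR reporting | Section 6.3 | to end of study |

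**Capture.** Hours in the objective without a scheduled entry: 24 − 12 = 12. As a share: 12 / 24 = 50%. In those hours section 6.2.1 relies on spontaneous reports by the patient or observation by staff, and section 6.2.2 on the investigator documenting SAEs. Events can still reach the database, but nothing in the form prompts anyone to look for them. Section 5.3 does not close the gap: its 12 hours refers to opioids, and it gives no window for (S)AEs.

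**Attribution.** The 12-hour rule can be tested against the text around it.

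1. Against the assessment in section 6.2.3: the investigator and the independent expert are to decide on a degree of probability. The rule replaces that judgement with certainty for every SAE that occurs after hour 12.
2. Against the list in section 6.2.2: the only reason for the rule is how long the drug works. Needle injury to a nerve and arterial puncture are events of the procedure, and the protocol nowhere ties them to drug duration. The Summary also names infection and permanent nerve injury as block risks, and the same holds for these.
3. Against section 6.2.2 on seriousness: persistent disability is one of the criteria, and persistence takes time to show.
4. Against section 6.3: SUSARs are reported to the end of the study, yet under the rule no SAE that occurs after hour 12 could become one.

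The rule is not needed to contain workload either. Sections 6.2.2 and 6.2.3 already exempt SAEs directly relatable to the hip fracture from portal reporting.

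**The case against.** The strongest reply is that late events are not lost. Section 6.2.1 records all AEs reported or observed during the study, section 6.2.2 has all SAEs documented without a time limit, section 6.3 follows AEs until they abate or stabilise, and section 8.1 seeks access to the patient record for the rest of the study period. Figure 2, which shows six data-collection points, is not reproduced, so a later time point cannot be excluded. This stands. It limits the claim to the absence of a scheduled entry in the form as shown.

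Four stronger readings are tempting and are not supported.

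- A reader might infer that the 12-hour rule biases the comparison of arms towards no harm. The endpoint in section 5.1.2 has no relatedness filter, so an SAE at 15 hours that is classed as unrelated would still count.
- A reader might infer that nerve injury is masked while the block works, leaving 0 to 4 hours of usable observation (12 − 12 = 0; 12 − 8 = 4). The protocol does not say this. It is a clinical inference, and it takes the rule's word for an event's occurrence to mean its detection. An injury caused at placement and noticed later might fall outside the rule. The text leaves that open.
- A reader might infer that late nerve injuries or bleeds would never be expedited. A SUSAR is defined as unexpected, these events are listed as known, and sections 6.2.2 and 6.2.3 blur SAR and SUSAR. What would be expedited is unclear even before 12 hours.
- A reader might apply the quoted 1-2% bleeding risk to 198 patients and obtain about 2 to 4 cases (198 × 0.01 = 1.98; 198 × 0.02 = 3.96). That figure covers any bleeding in all three arms. Nothing says that any of it appears after 12 hours.

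It can also be said that the form's LA question already covers puncture bleeding and nerve injury, because section 6.2.2 lists them as LA-related. That is a fair reading of the protocol's usage. The form's wording does not make it plain to the person who fills it in.

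**Conclusion.** The point holds in two parts. First, the 24-hour objective and the 12-hour form contradict each other: half of the comparison window has no scheduled (S)AE entry and is not systematically captured. This rests on Appendix IV as shown and would fall away if Figure 2 contained a later (S)AE time point. Second, the categorical 12-hour sentence overrides the case assessment in its own section and does not fit events that the protocol itself lists. This does not depend on any figure that is missing from the text.

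The first part affects the completeness of a low-event secondary comparison. The second affects relatedness classification and reporting to the ethics committee. Neither touches the QoR-15 endpoint or the sample size. The number of events at stake cannot be given from the protocol. This should be fixed, but it does not threaten the main result.

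**What to change.** - Reconcile the secondary objectives in section 1, the endpoint in section 5.1.2, the relatedness text in section 6.2.3 and the form in Appendix IV on one safety window, and state that window in each place.
- If 24 hours is kept, add an (S)AE entry by chart review at 24 hours in all three arms. Record the time of each event and whether surgery had taken place by then. The 12-hour page can stay for opioids.
- Replace the categorical 12-hour sentence in section 6.2.3 with the assessment by the investigator and independent expert that the section already describes. Time since the block can be one consideration among others.
- Word the attribution item in the form so that it asks about a link with the LA or the block procedure.

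The cost is an amendment to protocol and form wording, plus one later chart check per patient. There is one real drawback. All patients have a fracture that requires surgery, and the protocol foresees that some reach the operating room before 6-8 hours, so a 24-hour review will pick up post-operative events that need attribution. Recording event time and surgical status makes that attribution easier but does not remove the problem.
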